### **Statistical hypothesis**

It is expected that the administration of NASVAC TVC, as defined in the present protocol, to chronic hepatitis B patients, will improve the specific anti-HBV immune response of treated patients and consequently will significantly increase the percentage of patients reducing the viral load to undetectable levels after treatment completion compared to the group administered with Pegylated Interferon, expecting a difference between groups of more than 20%.

H0: Equivalency in the percentage of chronic hepatitis B patients reducing the viral load to undetectable levels. Formally,  $H_0: \delta \leq \delta_0 = 0.20$  where  $\delta$  represents the difference between viral seronegativization, based in quantitative PCR assay with a sensitivity of 250 copies/mL, in the group treated with NASVAC compared to the group treated with Interferon.

H1: Superiority in the percentage of chronic hepatitis B patients reducing the viral load to undetectable levels. Formally,  $H_1: \delta > \delta_0 = 0.20$  where  $\delta$  represents the difference between viral seronegativization, based in quantitative PCR assay with a sensitivity of 250 copies/mL, in the group treated with NASVAC compared to the group treated with Interferon.

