### **2.4 Reason for which the trial is carried out and background information about the vaccines**

In general, current treatments for CHB are limited in efficacy (around 30% on the basis of some particular criteria). Previous attempts to explore the efficacy of preventive commercial vaccines used for CHB active immunotherapy have also shown a limited efficacy. In this sense, the use of potent adjuvants, new antigens and more immunogenic formulations have been suggested to subvert the immunotolerant status in CHB patients.

The present active immunotherapeutic strategy has been designed to address this problem. This strategy comprises the use of the major HBs and HBc HBV antigens in a novel nasal formulation named NASVAC, characterized by an important cellular and humoral immunogenicity and by the ability to activate both the systemic as well as the mucosal immune compartments in animal models. The proposed approach is considered novel since it has been proven to induce a potent immune response in animal models improving the current state of the art on CHB TVC.

Importantly, NASVAC comprises two antigens:

- a) The r-HBsAg derived from the Cuban *Pichia pastoris* yeast strain transformed by genomic insertion of "s" gene to express r-HBsAg.

This antigen is molecularly identical to that derived from the *Saccharomyces cerevisiae* plasmid constructions used by most of the other vaccines. However, other features were also different for the active antigenic ingredient of the Cuban vaccine, such as a milder purification process (patented) designed to preserve HBsAg-r molecule integrity, including a unique step of preparative

immunoaffinity chromatography (on selective and specific monoclonal antibody). This process is now considered relevant for the higher immunogenicity shown by antigen in preclinical studies and clinical trials around the world. In this sense, the nasal formulation under study -NASVAC- receives the benefit of using the surface antigen with a higher immunogenicity.

- b) The r-HBcAg, the 183 aa. recombinant core antigen (HBcAg) purified and obtained from *E coli* as virus-like particles of around 28 nm with more than 95% purity.

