Virological response was assayed after five and ten doses. The HBeAg negative group of patients behaved better in terms of HBV elimination by quantitative PCR (detection limit 250 copies/mL) compared to HBeAg positive group. From 13 HBeAg patients receiving five intranasal doses of NASVAC, six patients reduced the viral load to undetectable levels for 46% just after five intranasal doses. None of the six patients clearing the virus were over the ULN for ALT after the fifth or after dose number 10, even when four of them had a mild ALT flare during the first cycle of IN administrations, suggesting a quick immune response. The absence of ALT increase during treatment in two patients clearing the virus suggests that non-cytolytic mechanisms were also activated. For patients clearing the virus, ALT increases ranged between 1.5 and 3 times the ULN, such increases where in one or two consecutive determinations only, suggesting that the potentially curative effect of vaccination was associated at least to small and quick flares of ALT levels. Such increases were not clinically apparent as patients didn't report any adverse event during the course of the vaccination, and physicians didn't detect any related symptom, suggesting that the increases in ALT levels were not clinically apparent. Also, due to the temporal relation to the starting date of the protocol, it is reasonable to predict that it was associated to the vaccination. From literature is known that specific immune stimulation has been related to ALT increases and virological response in CHB patients.

In support of the results obtained after the end of treatment, the evaluation of the 6 month time follow up (time 12 months) evidenced a further decrease in the levels of HBV DNA to undetectable levels in 50% of total patients, being outstanding the behavior of HBeAg negative patients that reduced the viral load in 8 of 13 patients. HBeAg positive patients also evidenced strong reductions in viral load however the reduction to undetectable was reduced compared to HBeAg negative patients, which is understandable based in the fact that the baseline viral load values were much higher for HBeAg positive patients. For both groups ALT values evidenced a generalized normalization reaching 100% at month 9 and 95% at month 12..

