Further clinical research is required as in case the concept of therapeutic immunization is probed, a large amount of world population will find in therapeutic vaccination a new finite and affordable treatment to overcome current situation.

*All previously presented facts induced the following **working hypothesis**:*

*The administration of NASVAC to CHB patients may subvert tolerance to the surface and core antigens (Ag) of HBV inducing specific immune responses (antibody seroconversion to anti-HBs and anti-HBe), T cells (Th1, CTL) and antigen presenting cells (APCs). Such immune response will favor the control of virus replication and will normalize the transaminases (ALT and AST) in a similar or superior extent to the currently approved treatment Interferon alpha 2b, associated to a lower number of adverse reactions.*

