### **Serology: Response:**

**HBeAg: Negativity:** disappearance from serum

**Seroconversion:** disappearance of HBeAg from serum and appearance of HBeAb.

**HBsAg: Negativity:** disappearance from serum

**Seroconversion:** Appearance of HBsAb in serum.

Both groups will be compared according to the categories defined above by the chi-square test or odds ratio calculation. A logistic regression will be also performed for a multivariate analysis of the influence of the different control variables that result significant in the previous univariate analysis. A signification level of  $p = 0.1$  will be considered. The potency will be of 80%.

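### The formal null already allows a 20-point advantage and no larger alternative is fixed, so the stated 80% power belongs to no stated effect, and the named chi-square test addresses a different null

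*Protocol*

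**What the plan says.** The hypothesis block appears twice with nearly the same wording, after section 2.3 (Specific objectives) and in section 10 (Statistics). The narrative has the trial "expecting a difference between groups of more than 20" per cent between NASVAC and interferon in the percentage of patients reaching undetectable HBV DNA. The null is described as "H0: Equivalency in the percentage of chronic hepatitis B patients reducing the viral load to undetectable levels" and then formalised as "H_0: \delta \leq \delta_0 = 0.20". The alternative is a difference above 0.20. No arm rates and no specific difference above 0.20 are given.

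The significance level (0.1), the power and the test all stand in section 10 under Serology: Response. There the protocol says "Both groups will be compared according to the categories defined above by the chi-square test or odds ratio calculation", and also "The potency will be of 80" per cent. It does not say whether 0.1 is one- or two-sided.

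Number of patients says the size was chosen in view of the hypothesis, but gives 60 per group and 180 in total. Design of the trial gives 160 patients in two groups, with 80 in the NASVAC group. The Interim analysis section uses a 20% advantage again, as a success threshold.

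Elsewhere, section 2.4 says that "current treatments for CHB are limited in efficacy (around 30% on the basis of some particular criteria"), and section 2.7 reports from the 20-patient NASVAC study a "further decrease in the levels of HBV DNA to undetectable levels in 50% of total patients" at 12 months. The working hypothesis in section 2.7 is that NASVAC acts "in a similar or superior extent to the currently approved treatment Interferon alpha 2b".

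**The concern.** A superiority margin and a planning effect do different jobs. The margin is the largest true advantage that still counts as failure; the planning effect is the true advantage at which the trial should succeed with the stated power. Here 20 points fills the first role and is also the only figure offered for the second. A test with level alpha rejects with probability alpha at the edge of its null, so 80% power is possible only at some difference well above 20 points, and the protocol names none.

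The words and the formula also disagree. Equivalency suggests no difference, while the formal null includes NASVAC being up to 20 points better.

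What is at stake is the meaning of a positive result. A significant chi-square test supports a difference from zero. Reported against the hypothesis as written, it could be taken as evidence of an advantage above 20 points, which it is not.

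**Working it through.** **Inputs from the protocol.** Margin 0.20; level 0.1, sidedness not stated; power 80%; per-arm sizes of 60 (Number of patients), 80 (Design of the trial) and 180/2 = 90 (Number of patients, total split over two groups).

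**Assumptions.** Control rate 30%, with 10–40% or 10–50% as a range; NASVAC rate 50% where a pair is needed. The protocol does not state these as design rates.

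**Can the stated 80% be reproduced?** Not under the formal hypothesis, because no alternative is given. For a null of zero at 30% v 50%, with the pooled standard error under the null:

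power = Φ[(0.20 − z·SE0)/SE1], SE0 = √(2·0.4·0.6/n), SE1 = √((0.3·0.7 + 0.5·0.5)/n).

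At n = 80, SE0 = 0.0775 and SE1 = 0.0758. At two-sided 0.10, (0.20 − 1.645·0.0775)/0.0758 = 0.957, giving 83%.

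| Null of zero, 30% v 50% | n = 60 | n = 80 | n = 90 |
|---|---|---|---|
| two-sided 0.10 | 73% | 83% | 87% |
| two-sided 0.05 | 61% | 74% | 79% |
| one-sided 0.10 | 84% | 91% | 93% |

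The size needed for 80% is 54 per arm (one-sided 0.10), 74 (two-sided 0.10) or 93 (two-sided 0.05). None matches 60, 80 or 90, although 80% power is in reach in this region.

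**Power against the 0.20 margin.**

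power = Φ[(δ − 0.20)/SE − z(1−α)], SE = √((pc(1−pc) + pt(1−pt))/n).

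At δ = 0.20 the first term is zero, so power = Φ(−z(1−α)) = α for every n and every pair of rates: 10% at one-sided 0.10, 5% if 0.1 is two-sided.

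At δ = 0.25, pc = 0.30, n = 80: SE = √((0.21 + 0.2475)/80) = 0.0756, and 0.05/0.0756 − 1.282 = −0.62, giving 27%.

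| Control 30%, one-sided 0.10 | n = 60 | n = 80 | n = 90 |
|---|---|---|---|
| power at 20 points | 10% | 10% | 10% |
| power at 25 points | 24% | 27% | 28% |
| power at 30 points | 45% | 52% | 55% |
| difference needed for 80% power | 38 points | 36 points | 35 points |

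At 80 per arm, over control rates of 10–40%, the difference needed for 80% power is 34–36 points at one-sided 0.10, 36–38 at one-sided 0.05 and 38–40 at one-sided 0.025.

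**The ordinary chi-square test at the edge of the null.** I summed binomial probabilities over all tables in which the pooled z statistic favours NASVAC and exceeds 1.645 (two-sided 0.10). At true rates of 30% v 50%, which lie on the null boundary, the test rejects with probability 75%, 82% and 88% at 60, 80 and 90 per arm. Over control rates of 10–50%, with a true difference of 20 points throughout, the range is 73–97%.

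An example at 80 per arm: 24/80 v 35/80 is an observed difference of 11/80 = 13.75 points. The pooled rate is 59/160 = 0.369, SE = √(2·0.369·0.631/80) = 0.0763 and z = 0.1375/0.0763 = 1.80, significant at two-sided 0.10. The observed difference does not even reach the margin.

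**The case against.** A superiority margin is a legitimate choice, and the reuse of 20% as an interim success threshold suggests it may be deliberate. The protocol also expects more than 20 points, so power equal to alpha is the value at the bottom of the expected range. Both points stand. A reader might infer that the trial's power simply is alpha, or that it is almost certain to fail even if NASVAC does as well as hoped. The documents do not support that: a true difference of about 36 points would give 80% power at 80 per arm under the assumptions above.

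A reader might also take 30% and 50% as the protocol's own planning rates. They are not. The 30% describes current treatments by unspecified criteria and is not tied to undetectable HBV DNA under pegylated interferon; the 50% comes from a 20-patient study. Other figures appear too, such as 8 of 13 HBeAg-negative patients in the same study. The two rates serve only as assumptions here, and the result at the margin does not depend on them.

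The level, the power and the test are printed under Serology. Reading the categories defined above as including HBV DNA response is reasonable but not explicit. Nor does the protocol say that a significant chi-square test will establish a difference above 0.20, so the 75–88% is conditional on that use. An unseen analysis plan might name a margin test, but it would not supply the missing alternative behind the protocol's own power statement.

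Finally, the working hypothesis of similar or superior effect is broad and also covers transaminases, so it does not refute the margin.

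**Conclusion.** The point holds in this limited form: the formal null, the expected effect, the stated power and the named test do not fit together. The margin equals the lower bound of the expected effect and nothing above it is specified, so 80% power cannot be verified under the hypothesis as written. That conclusion needs no assumed rates. Its size does: with 30% control response and one-sided 0.10, power is roughly a quarter at 25 points and about a half at 30. The test mismatch rests on applying the Serology paragraph to HBV DNA and on using its result to claim the formal alternative. It should be corrected before analysis, because it concerns the hypothesis on the main efficacy variable and determines what a positive result may claim.

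**What to change.** **Preferred.** In both copies of the Statistical hypothesis, restate the null as a difference of 0 or less, described as no superiority in place of equivalency, against a difference above 0. Keep 20 points only as the planning difference. Name, for HBV DNA undetectability explicitly, a test of that null, and report the difference with its confidence interval. State the assumed arm rates, alpha and sidedness. First reconcile Design of the trial with Number of patients, then give the power for the single size that remains. For an assumed 30% v 50%, that is 73/83/87% at two-sided 0.10 or 61/74/79% at two-sided 0.05, for 60/80/90 per arm.

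**Alternative.** Keep the 0.20 margin and require the lower confidence limit for the difference to exceed 0.20. State the arm rates, and say that at 80 per arm and control rates of 10–40%, 80% power needs a true difference of about 34–36 points (one-sided 0.10) to 38–40 points (one-sided 0.025).

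**Cost.** Both are changes of wording. Whether more patients are needed depends on the reconciled size and on alpha: at 60 per arm neither two-sided level reaches 80% power, and at two-sided 0.05 none of the three sizes does. Under the first option the claim becomes superior rather than superior by more than 20 points. Under the second the power statement becomes less favourable.

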### **Serology: Response:**

**HBeAg: Negativity:** disappearance from serum

**Seroconversion:** disappearance of HBeAg from serum and appearance of HBeAb.

**HBsAg: Negativity:** disappearance from serum

**Seroconversion:** Appearance of HBsAb in serum.

Both groups will be compared according to the categories defined above by the chi-square test or odds ratio calculation. A logistic regression will be also performed for a multivariate analysis of the influence of the different control variables that result significant in the previous univariate analysis. A signification level of  $p = 0.1$  will be considered. The potency will be of 80%.

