### **2.3 Specific objectives**

With the above mentioned purpose the following specific objectives are declared:

1. To evaluate the immunogenicity resulting from the application of the NASVAC TVC to CHB patients, assessing the effect of intranasal / subcutaneous administration on the induced humoral and cellular immune response and finally on the viral load as a variable dependent on immune response, that will be used as the main variable.
2. To identify possible adverse events (AE) linked to the application of the NASVAC TVC to CHB patients and assess their frequency and intensity in the scenery of intranasal/subcutaneous administration.
3. To collect and assess preliminary data on the therapeutic potential of the NASVAC TVC in CHB patients regarding to:
  - Reduction of the serum HBV DNA levels.
  - HBsAg / HBeAg clearance and anti-HBsAg / HBeAg seroconversion
  - Reduction in the levels of transaminase (ALT) activity
  - Clinical outcome of patients (as defined in the corresponding section)

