## **2.7 Clinical experience**

### ***NASVAC administration to healthy volunteers was safe and immunogenic***

A Phase I Placebo controlled study was conducted with NASVAC in order to evaluate the safety and immunogenicity in 20 human healthy volunteers. NASVAC evidenced a very good safety profile, comparable with the placebo used in the study: saline solution.

The immunogenicity of NASVAC was also evidenced in the same study: All vaccinated volunteers (100%) responded to HBcAg, in the case of the anti-HBsAg, 75% of the volunteers generated a seroprotective response and 50% of those were hyper-responders (more than 100 UI/L of anti HBsAg antibodies). There was no immune response against any of the antigens in the placebo group (see corresponding Annex).

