### 5.3 Inclusion criteria

- HBsAg+ serology for more than 6 months before the beginning of the treatment.
- HBeAg (-) patients, with a) baseline HBV DNA  $\geq 10^3$  and b) raised serum ALT ( $> 1 \times \text{ULN}$ ) or significant hepatic necro-inflammation and or fibrosis (HAI-NI $\geq 4$  and/or HAI-F  $\geq 2$ ), or stiffness  $> 7.2$ .
- HBeAg (+) patients, with a) baseline HBV DNA  $\geq 10^4$  and b) and raised serum ALT ( $> 1.5 \text{ ULN}$ ) or significant hepatic necro-inflammation and or fibrosis (HAI-NI $\geq 4$  and/or HAI-F  $\geq 2$ ) stiffness  **$> 7.2$** .
- 18 to 60 years-old patients of both sexes.
- No specific hepatitis B treatment at least for 6 months previous to the inclusion
- Voluntary signed informed consent to participate in the trial

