### **Interim analysis**

After 5 and 10 administrations and also at 48 weeks, patients will be tested by PCR to quantify HBV DNA in serum as well as for HBsAg and HBeAg seroconversion. A comparative study will be conducted for the same variables for internal comparisons between both groups in order to have a reference to standard treatment with a recognized efficacy.

a) A 20% superior percentage of viral load reduction to undetectable levels in the group treated with NASVAC compared to PegIFN treated group in any of the virological study cuts will be considered as a success criteria for the Interim Analysis.

b) A superior difference in the proportion of patients with ALT normalization or combined ALT normalization and viral load reduction to undetectable levels at a defined time (5, 10 dosis or 48 weeks) between groups will be considered a success criteria for the Interim Analysis.

e) A sustained biochemical (ALT) response during three consecutive determinations after dose number 10 will be considered a success criteria.

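### HBsAg seroconversion is defined by anti-HBs alone, so vaccine-induced antibody can count as a serological response in a patient who remains HBsAg-positive

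*Protocol*

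**What the plan says.** The Serology: Response paragraph of section 10 defines two categories for each antigen.

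- **HBeAg.** Negativity is disappearance from serum. Seroconversion has two parts: "disappearance of HBeAg from serum and appearance of HBeAb".
- **HBsAg.** Negativity is again disappearance from serum. Seroconversion has one part: "Appearance of HBsAb in serum".

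The paragraph continues: "Both groups will be compared according to the categories defined above by the chi-square test or odds ratio calculation". It then names a significance level of 0.1 and power of 80%.

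The outcome appears in two other places. Section 2.3, objective 3 (preliminary data on therapeutic potential) lists "HBsAg / HBeAg clearance and anti-HBsAg / HBeAg seroconversion". The Interim analysis paragraph has patients tested after 5 and 10 administrations and at 48 weeks for HBV DNA "as well as for HBsAg and HBeAg seroconversion".

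On the product and the patients, section 2.4 says: "This strategy comprises the use of the major HBs and HBc HBV antigens in a novel nasal formulation named NASVAC". The control group receives pegylated interferon (section 6, Treatment schedule). Patients enter with "HBsAg+ serology for more than 6 months before the beginning of the treatment".

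**The concern.** The HBeAg definition shows that this protocol writes antigen loss into a definition when it wants it. It is absent for HBsAg, and nothing elsewhere supplies it.

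The omission matters more here than in a comparison of two antiviral drugs, because one arm is given the antigen to which the scored antibody is directed and the other is not. Antibody raised by vaccination would show that the vaccine is immunogenic, which is the subject of objective 1. As written, the same antibody also counts as seroconversion under objective 3. A table with HBeAg and HBsAg seroconversion in adjacent rows would invite the reader to take them as the same kind of event. A between-group difference in the HBsAg row could then be read as therapeutic benefit although no patient had lost HBsAg.

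**Working it through.** The protocol states no figure for this outcome, so there is nothing to reproduce. The check has two parts.

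**1. What the definition allows**

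| HBsAg at follow-up | Anti-HBs at follow-up | HBsAg negativity | HBsAg seroconversion as written | Under a definition parallel to HBeAg |
|---|---|---|---|---|
| absent | present | yes | yes | yes |
| absent | absent | yes | no | no |
| present | present | no | **yes** | no |
| present | absent | no | no | no |

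Only the third row is affected. Whether it can be filled mainly in one arm depends on these facts:

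- All patients are HBsAg-positive at entry (section 5.3).
- NASVAC carries HBsAg (section 2.4; section 6 gives 50 µg per 0.5 mL).
- Section 2.7 reports that in healthy volunteers "75% of the volunteers generated a seroprotective response", and that the placebo group had no immune response to either antigen. Vaccination alone can therefore produce the antibody.
- Section 2.6.3 reports humoral responses in all transgenic mice, which express HBsAg constitutively, after at least 5 doses by the two routes. This supports plausibility in a host that carries the antigen, but it is mouse data.
- No anti-HBs rate is given for chronic hepatitis B patients. Section 2.7 describes the earlier patient study through HBV DNA and ALT.

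**2. How large a difference could arise with no HBsAg clearance**

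All anti-HBs rates below are assumptions. For a responders out of n on NASVAC and b out of n on interferon, uncorrected chi-square = 2n·[a(n−b) − b(n−a)]² / [n²·(a+b)·(2n−a−b)].

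With 80 per group (section 4) and 2/80 = 2.5% on interferon:

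- 8/80 (10%): 160 × (8×78 − 2×72)² / (6400 × 10 × 150) = 160 × 480² / 9,600,000 = 3.84, p = 0.050
- 16/80 (20%): 160 × 1120² / (6400 × 18 × 142) = 12.27, p = 0.0005
- 24/80 (30%): 160 × 1760² / (6400 × 26 × 134) = 22.23, p < 0.0001

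Dependence on the test variant:

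| NASVAC vs interferon | Uncorrected | Continuity-corrected | Fisher's exact |
|---|---|---|---|
| 8/80 vs 2/80 | 0.050 | 0.102 | 0.098 |
| 16/80 vs 2/80 | 0.0005 | 0.001 | 0.0007 |
| 24/80 vs 2/80 | <0.0001 | <0.0001 | <0.0001 |

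The Number of patients paragraph gives 60 per group instead. There 2.5% is 1.5 patients, so a whole number must be chosen. For 10% on NASVAC, 6/60 vs 2/60 gives uncorrected p = 0.14. 6/60 vs 1/60 gives 0.051 uncorrected, 0.119 corrected and 0.114 by Fisher's exact test.

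As a probability, power = Φ[(d − 1.645·se0)/se1], two-sided at 0.10, with se0 from the pooled proportion and se1 from the separate proportions. For 20% vs 5% at 80 per group: d = 0.15, se0 = √(0.125 × 0.875 × 2/80) = 0.0523, se1 = √[(0.16 + 0.0475)/80] = 0.0509. The argument is (0.15 − 0.0860)/0.0509 = 1.26, so power is about 90%. The same formula gives 81% at 60 per group. For 10% vs 5% it gives 33% at 80 per group and 27% at 60.

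**The case against.** The strongest reply is that the same paragraph already guards against the misreading. HBsAg negativity is its own category and is compared between groups, so an absence of clearance would appear beside any seroconversion difference. This stands and limits the weight of the point. It does not remove it, because the seroconversion category is compared in its own right without requiring negativity.

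Second, no decision rests on the outcome. The main variable is HBV DNA, the hypothesis concerns undetectable HBV DNA, and the lettered success criteria in the Interim analysis paragraph use HBV DNA or ALT. A reader might infer from the interim testing of seroconversion that it could trigger a claim of success. The document does not support that.

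Third, the protocol elsewhere uses anti-HBs seroconversion as an immune-response term (section 2.4 and the working hypothesis in section 2.7), which fits an antibody-only reading. That is fair, and objective 3 calls its data preliminary and names clearance separately. But objective 3 still places seroconversion under therapeutic potential, so part of the confusion with objective 1 remains.

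Fourth, a reader might infer that the arms must differ on this endpoint because of what the vaccine contains. That is not shown. The 75% comes from healthy volunteers in a 20-person phase I study. The protocol's premise is that patients are tolerant to HBsAg, and it gives no patient rate.

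Fifth, the 0.1 level follows the sentence on logistic regression and may be meant for screening variables there rather than for the group comparison. The 20% and 30% cases at 80 per group are also below 0.05, so they do not depend on this. The 10% case does.

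**Conclusion.** The definition is wrong as written for a therapeutic outcome. It can score a response in a patient who still carries HBsAg, and it is inconsistent with the HBeAg definition in the same paragraph. This rests on the text alone and needs no assumed rate.

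The size in this trial is unknown. If 20% or 30% of NASVAC patients and 2.5% of interferon patients developed anti-HBs with HBsAg persisting, the comparison at 80 per group would be clearly significant under every test variant tried. At 10% it would be borderline and would depend on the variant and the group size.

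The effect is confined to a secondary serological outcome and how it is labelled and interpreted. It does not touch the HBV DNA hypothesis, the interim success criteria or the separate comparison of HBsAg negativity. It is worth correcting, but it does not threaten the main conclusion.

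**What to change.** In section 10, Serology: Response, replace the HBsAg seroconversion line with a two-part definition parallel to HBeAg: *HBsAg seroconversion: disappearance of HBsAg from serum and appearance of HBsAb.* Report anti-HBs appearance without HBsAg loss as a separate immunogenicity variable under objective 1, not as a treatment response. Read objective 3 and the Interim analysis paragraph with the revised definition.

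The cost is one line and one extra descriptive row. HBsAg and anti-HBs are both already in the schedule of determinations, so no new test is needed. The shading that marks omitted visits is not visible in the text at hand, so the sponsor should confirm that both are measured at the visits where seroconversion is assessed. The downside is a lower reported HBsAg seroconversion rate if some patients develop antibody without losing the antigen.
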